## Methods

### Study design

This study is a partially randomized controlled trial. Clients will be randomly assigned to one of two groups. An additional intervention group (IG 1) will be generated from an existing archival data set via propensity score matching.Control group (CG): Treatment with continuous assessments but without computer based feedback to therapists.Intervention group 1 (IG1): Patients in this group received treatment with continuous assessments including computer-based feedback to therapists after each session. This group is a matched sample.Intervention group 2 (IG2): Treatment with continuous assessments including computer based prediction as well as feedback/adaptation tools to therapists after each session including an alarm for NOT patients.

The project was submitted to and approved by the Ethics Committee of the University of Trier. Since it is a non-invasive procedure, patients are informed about data protection law consequences and their opportunity to refuse to accept the storage and use of video data for research purposes at any time. An explanation of the various experimental conditions will be given at the end of the project.

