### Randomization

First, patients will be randomly assigned to therapists after the SCID-I interview which will be conducted by an independent trainee (see Fig. 2). Second, patients will be randomized to one of two groups (CG or IG2). This means that the same therapist treats patients who are in the CG as well as patients who are in the IG2. The assignment procedure of patients to therapists will secure, that each therapist will treat at least eight patients and that each therapist has patients in both conditions. As an additional randomization condition a matching procedure is applied, which ensures that the therapists do not differ in terms of their level of clinical experience and years of using the feedback system in IGs and the CG. A second intervention group (IG1) is generated via propensity score matching from already existing archival data set based on diagnoses, intake severity as well as social-demographic variables like age and gender.

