### Sample size calculation and data analyses

Since the two main hypotheses are based on pairwise comparisons of the NOT patients, the sample size calculation was done so that the size of these comparisons have sufficient power (1-β = .8). Power analyses for the main hypotheses have been conducted with GPower 3.1 [47]. Hypothesis 1 postulates a superior treatment outcome for NOT patients in the IG1 compared to the CG. The average effect for feedback in NOT patients compared to treatment as usual found in the literature is between *r =* .25 [17]. To find this effect in a two-way repeated measures ANOVA with (feedback yes/no) and assessment time (pre/post) with a power of at least 80%, an a priori significance level of .05, and a correlation between assessments of .4, the sample has to include at least *N* = 38 NOT patients in total (IG1 and CG). The incremental effect for feedback with CSTs in comparison with feedback without CSTs was *d =* .31 [48]. We therefore assume a small incremental effect (*d =* .30) for the use of CST in this project. To find this effect in a two-way ANOVA with (feedback yes/no) and assessment time (pre/post) with a power of at least 80%, an a priori significance level of .05, and a correlation between assessments of .4, the total sample has to include *N* = 108 NOT patients in total (IG 1 and IG 2). To make sure, that treatment groups and CST are more comparable with respect to the number of patients, we added for the sample size calculation in the CG half of the NOT patients in IG1/IG2, resulting in at least 27 NOT patients for the CG.

In a previous study the proportion of patients who received at least one alarm signal within the first 8 sessions was approximately 49% [49]. Also, Simon et al. found that 56% of the patients were NOT and therefore received an alarm signal [22]. For our sample size calculation we used a more conservative estimate of 40% of NOT patients, which results in a total sample size of *N* = 338 (CG = 68, IG = 135, IG2 = 135). In order to control for drop-out, we added a puffer of 25% to the required sample size to make sure the power analysis is valid. The described procedure above, results in final sample sizes for each group shown in Table 2.

**Table 2 Tab2:** Intended recruitment and sample size of treatment groups

Treatment	Sample size
Intervention group 1	169
Intervention group 2	169
Control group	85

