Three moderators and two mediators of the feedback effect will be investigated in hypotheses 3 and 4 (see also Fig. 1): Moderators: therapists’ attitudes towards feedback, feedback usage and diagnoses; Mediators: Therapists’ awareness for negative developments and treatment length. In order to control for therapist effects, therapists will be modelled as random effects at level two.

Therefore, *Optimal Design Software for Multilevel and Longitudinal Research* (Version 3.01; [50]) was used to determine the minimal effect that can be detected with sufficient power, given the sample size calculation above. Assuming a therapist effect of 5% and k = 50 therapists delivering the treatments to j = 8 patients each, a small effect (d = .2) can be detected with sufficient power (1-β = .8). Thus, given the sample size calculated for the primary hypotheses, the secondary analyses can be conducted with sufficient power using multi-level models (e.g., [51]). Ensuring the stability of the results, all analyses will be checked with Mplus software (e.g., [52]).

Additional Monte Carlo simulations with Mplus (Version 7; [52]) were run to specifically test the mediation models from hypotheses 3 and 4. Assuming again small effects for the direct associations, 10,000 datasets have been simulated with the actual sample size of the study sample. These simulations revealed a sufficient power of 1-β = .874. Thus, given the sample size calculated for the primary hypotheses, the mediation analyses can also be conducted with sufficient statistical power to detect indirect mediation effects adjusting for above described control variables.

Furthermore, the analyses will be controlled for the following potential influencing factors: comorbidity (number of additional diagnoses, additional personality disorders), initial impairment, clinical experience as well as experience with the feedback system.

Finally, the data of the project will have a hierarchical data structure because patients will be nested within therapists. Two-level hierarchical models will be applied to the data to correct for therapist influences [51].

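### The multilevel power for the secondary hypotheses (50 therapists × 8 patients) does not describe the randomised part, where the protocol's own caseload rule allows at most 31 therapists, and the stated 80% at d = .2 does not reproduce

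*Protocol article*

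**What the plan says.** All references are to the Protocol article.

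- **Sample size calculation and data analyses**, on the secondary hypotheses: multilevel software "was used to determine the minimal effect that can be detected with sufficient power, given the sample size calculation above". The inputs are: "Assuming a therapist effect of 5% and k = 50 therapists delivering the treatments to j = 8 patients each". The result is that "a small effect (d = .2) can be detected with sufficient power (1-β = .8"). The article concludes that the secondary analyses are adequately powered.
- **Same section**, on the primary hypotheses: the required sample before the drop-out buffer is 338 ("CG = 68, IG = 135, IG2 = 135"). With the 25% buffer this becomes 169 + 169 + 85 = 423 (Table 2). The primary calculations use "an a priori significance level of .05". No alpha, sidedness, design type or covariate is given for the multilevel calculation.
- **Randomization**: "patients will be randomized to one of two groups (CG or IG2"). The assignment procedure is to secure that "each therapist will treat at least eight patients and that each therapist has patients in both conditions".
- **Study design**: "An additional intervention group (IG 1) will be generated from an existing archival data set via propensity score matching".
- **Assessment of feedback related variables**: therapists' attitude towards feedback is measured when a therapist begins work in the project.

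**The concern.** The power statement multiplies out to 400 patients, while the trial assigns only 254 to therapists. The rest of the 423 come from archived treatments. If the 50 therapists are meant to be those of the randomised comparison, the number conflicts with the eight-patient rule. If they include therapists known only from the archive, those therapists contribute no within-therapist contrast between randomised conditions and may lack the attitude score that H3 and H3b need. The article does not say which is meant.

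The Background criticises earlier work because moderators and mediators were studied without a dedicated power analysis, so this calculation is presented as an advance. If the real detectable effect is well above d = .2, a null moderator or mediator result could be read as evidence of no effect when the trial could not have seen one.

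**Working it through.** **1. The sample-size chain.** The 108 patients not on track give 54 per intervention group, and 54/.4 = 135. The 27 in the control group give 27/.4 = 67.5, rounded to 68. Total: 135 + 135 + 68 = 338. Multiplied by 1.25: 169, 169 and 85, total 423. The chain reproduces.

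**2. Caseload bound.** The rule is at least 8 patients per therapist, so the maximum number of therapists is N/8 rounded down.

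| Patients counted | N | N/8 | Most therapists |
|---|---|---|---|
| CG + IG2, recruited | 85 + 169 = 254 | 31.75 | 31 |
| CG + IG2, before buffer | 68 + 135 = 203 | 25.4 | 25 |
| All three groups, before buffer | 338 | 42.25 | 42 |
| All three groups, recruited | 423 | 52.9 | 52 |

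The stated 50 × 8 = 400 fits only the last row. Fifty therapists sharing 254 patients would average 254/50 = 5.1 each, below the rule. If 31 therapists meet the rule in the randomised part, at least 50 − 31 = 19 must come from the archive alone. At 8 patients each they need 152 of the 169 archival patients, which is numerically possible.

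**3. The stated power.** Inputs: J therapists, n patients each, therapist effect ρ = .05, outcome SD 1, d = .2. Two-sided alpha .05 is assumed. Power is from the noncentral t with d/√v. The design type is not stated, so three were tried, with equal allocation:

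- (a) conditions crossed within therapist: v = 4(1 − ρ)/(Jn)
- (b) as (a), with an assumed variance of .05 in the effect across therapists: v = (.05 + 4(1 − ρ)/n)/J
- (c) therapists as clusters: v = 4(ρ + (1 − ρ)/n)/J

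For 50 × 8:

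- (a) v = 3.8/400 = .0095, SE .097, power .53
- (b) v = (.05 + .475)/50 = .0105, SE .102, power .48
- (c) v = 4(.05 + .11875)/50 = .0135, SE .116, power .39

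One-sided, these become .66, .61 and .52. Using the pre-post correlation of .4 as a covariate in (a) (R² = .16) gives .61 two-sided and .72 one-sided. None reaches .80. Model (a), two-sided, would need a covariate R² of about .47, which the article does not mention. The smallest detectable d with 80% power is .27 (a) to .33 (c).

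**4. The randomised part.** Two-sided:

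| Structure | Power at d = .2: (a), (b), (c) | Detectable d: (a), (b), (c) |
|---|---|---|
| 50 × 8 | .53, .48, .39 | .27, .29, .33 |
| 31 × 8 | .36, .32, .26 | .35, .38, .43 |
| 25 × 8 (before buffer) | .30, .26, .21 | .39, .42, .48 |

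With the actual unequal groups in model (a), SE = √(.95(1/169 + 1/85)) = .130 and the detectable d is about .36. For 135 v 68 it is about .41.

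**5. Counting the archive.** For all feedback patients against controls, 338 v 85 in model (a), SE = √(.95(1/338 + 1/85)) = .118, power at d = .2 is about .39, and the detectable d is about .33.

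**6. Therapist-level predictors.** These are on a different scale (outcome SD per predictor SD) and must not be compared with d = .2. SE = √((.05 + .95/n)/k). The slope detectable with 80% power is about .17 for 50 × 8, .21 for 31 × 8, and .30 for 31 therapists with .4 × 254/31 = 3.3 not-on-track patients each.

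**7. The not-on-track subset.** At 40%, eight patients become 3.2 per therapist. Fifty therapists then give power .22 to .25 at d = .2 and a detectable d of .44 to .48 across (a) to (c).

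**The case against.** A reader might infer that 50 × 8 is impossible in this trial. The documents do not support that. The multilevel statement refers back to the three-group calculation, intervention group 1 is a feedback arm, and H3 and H4 concern the effect of feedback, so counting its patients is a natural reading. On that reading 52 therapists with eight patients each are possible. This stands, and the point is therefore limited to the randomised part and to what counting the archive entails.

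Three further objections stand in part.

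- The figure 338 is the required size before the drop-out buffer. The article does not say that drop-outs leave the analysis, so 400 exceeding 338 is a mismatch with the required sample and not by itself an error.
- The software's design type, allocation and covariates are unstated, and the Discussion even calls the trial cluster randomised. The shortfall at 50 × 8 may therefore reflect unseen settings. The three models cover the plausible designs, but only the authors can settle this.
- The control group of 85 limits the feedback contrast more than the therapist count does: leaving out the archive moves the detectable d only from about .33 to .36.

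What the objection does not do is restore the stated figure. The pooled reading needs 19 or more archive-only therapists, who have no patients in both randomised conditions, whose contrasts lie between therapists, and whose attitude scores are not shown to exist. The pooled contrast in step 5 still falls well short of 80%.

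**Conclusion.** The concern holds in limited form. The 50 × 8 inputs do not describe the randomised comparison, which can have at most 31 therapists under the protocol's own rule. They match only the full recruited sample including the archival group.

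At d = .2, power in the randomised part is about .26 to .36 against the stated .80, and the detectable effect is roughly d = .35 to .43. The stated inputs themselves give about .39 to .53, so correcting the therapist count alone would not explain the discrepancy.

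These figures rest on a 5% therapist effect, a two-sided alpha of .05 (assumed), no covariates and, in one model, an assumed effect variance of .05. One-sided testing raises them but does not reach .80.

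A reader might also infer that the secondary analyses have no useful power or that the primary sample sizes are wrong. Neither follows: effects of about d = .36 and above remain detectable in the whole randomised sample under model (a), and the H1 and H2 calculations use neither the number of therapists nor the caseload.

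**What to change.** 1. State whether the 50 therapists include those who treated only archival patients, and whether any therapists overlap between the archive and the trial.
2. Make the therapist number agree with the eight-patient, both-conditions rule.
3. Recompute with the real structure: at most 31 therapists and 254 prospective patients (203 before the buffer), allocated 1:2 control to intervention group 2 within therapist. Treat any archive-only therapists as a separate between-therapist set.
4. Report the software settings: design type, alpha and sidedness, allocation, and any covariate with its assumed R².
5. Give the detectable effects separately for patient-level contrasts, therapist-level moderators and the not-on-track subset (about 40%), and withdraw the claim of adequate power where it does not hold.

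The cost is a short recalculation and a reworded paragraph. No extra enrolment is needed. The downside is that the stated detectable effects will become larger.

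### The stated inputs (50 therapists x 8 patients, 5% therapist effect) give about 39% to 61% power for d = .2, not 80%, and 400 is not the NOT sample that H3 and H4 concern

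*Protocol article*

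**What the plan says.** All of this is in the protocol article.

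- **Secondary power.** Under Sample size calculation and data analyses, the smallest detectable effect is derived for a 5% therapist effect and "k = 50 therapists delivering the treatments to j = 8 patients each, a small effect (d = .2) can be detected" with power .8. The article concludes that, "given the sample size calculated for the primary hypotheses, the secondary analyses can be conducted with sufficient power". It gives no covariate R² and no sidedness for this calculation.
- **Mediation.** The same section reports a separate Monte Carlo run that assumes small effects: "These simulations revealed a sufficient power of 1-β = .874". The path values and the simulated N are not stated.
- **Sample.** "For our sample size calculation we used a more conservative estimate of 40% of NOT patients", giving 338 patients (68 CG, 135 IG1, 135 IG2), raised by 25% to 423 (85, 169, 169).
- **Population.** Under Objectives, H3, H4 and H4a are worded for NOT patients. Under Assessment of therapists' awareness of negative change, the awareness variable used in H3a, H3b, H4a and H4b is computed only while a patient is NOT.
- **Assignment.** Under Randomization, CG and IG2 are allocated within therapist. IG1 is a matched archival sample. The Discussion nevertheless calls the trial cluster randomised.

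**The concern.** A two-group comparison at d = .2 needs 393 patients per group (786 in all) for 80% power even without clustering. A claim to reach that power with 400 patients in total, and a therapist effect besides, is therefore doubtful on its face. The figure is also presented as following from the primary sample size calculation, which is built on NOT patients, while 400 is close to the full enrolment.

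The stake is interpretation. The Background criticises earlier work for studying moderators and mediators without dedicated power analyses, so adequate power is part of what the article offers. H3c predicts no difference between diagnostic groups. A non-significant result there could be taken as support if readers believe that small effects were detectable.

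**Working it through.** **Inputs.** J = 50 therapists, n = 8 patients each, therapist effect ρ = .05 and d = .2, all from the sample size section. Alpha .05 is stated there for the main hypotheses. I assume it is two-sided and that arms are equal. The only covariate information is the pre/post correlation of .4, so R² = .4² = .16.

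**Step 1: the plan's own figure (noncentral F)**

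- Condition within therapist: λ = J·n·d² / [4(1−ρ)(1−R²)].
  - R² = 0: λ = 400 × .04 / (4 × .95) = 4.21, power .52 (49 df) to .53 (349 df).
  - R² = .16: λ = 4.21 / .84 = 5.01, power .59 to .61.
- Condition between therapists: λ = J·d² / {4[ρ + (1−ρ)/n]} = 50 × .04 / (4 × .16875) = 2.96, with 48 df, power .39.

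The stated .80 is not reproduced.

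**Step 2: detectable d at 80% power for 50 x 8 (multiplier about 2.8)**

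- Within therapist: SE = √(4 × .95 / 400) = .0975, d = .27.
- Within therapist, R² = .16: SE = .0975 × √.84 = .0893, d = .25.
- Between therapists: SE = √(4 × 1.35 / 400) = .116, d = .33 (using 48 df).

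Reaching .80 at d = .2 with eight patients each takes about 94 therapists (752 patients) within therapist, or 135 (1,080) between therapists.

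**Step 3: what would rescue the figure**

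- One-sided test, within therapist: .65 to .66, or .71 to .72 with R² = .16.
- No clustering at all: .52.
- A patient-level R² of about .47 to .49 (correlation about .69) reaches .80 within therapist. The article states no such value, and its own correlation implies .16.

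**Step 4: the NOT sample**

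At 40%: .4 × 338 ≈ 135 analysed (27 CG, 54 IG1, 54 IG2), or .4 × 423 ≈ 169 enrolled. At the 49% and 56% rates that the article cites, 423 patients yield 207 and 237, still far below 400.

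SE = √[.95 × (1/n₁ + 1/n₂)], multiplied by √.84 with the covariate:

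| Comparison (analysed NOT patients) | SE | Detectable d | With R² = .16 |
|---|---|---|---|
| IG1+IG2 vs CG, 108 vs 27 (1:4, includes archival IG1) | .210 | .59 | .54 |
| IG2 vs CG, 54 vs 27 (1:2, randomised) | .230 | .64 | .59 |

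For 108 vs 27, power at d = .2 is about .16, or .18 with the covariate. If every enrolled NOT patient were analysed (135 vs 34), the detectable d would be .48 to .52. Even an R² of .48 would leave 108 vs 27 at 2.8 × .210 × √.52 = .42.

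**Step 5: mediation**

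The .874 cannot be recomputed without the paths and N. For orientation, I assume a simple two-path model, joint significance and equal standardised paths, with power the product of the two path powers:

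- Paths of .10 / .14: .29 / .68 at n = 423, and .06 / .19 at n = 169.
- Paths of .20: .80 at n = 254, .92 at n = 338, .97 at n = 423, but .42 at n = 135 and .55 at n = 169.

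**The case against.** The recruitment target rests on H1 and H2. The disputed sentence only asks what that sample can detect, and H3 and H4 are already labelled secondary, so no recruitment figure or primary comparison changes. This stands and limits the weight of the point, but the stated power is still wrong.

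A different effect-size convention might lie behind the claim. With the repeated-measures setting f = d/2 = .10 and correlation .4, N = 400 gives .95. That calculation has no therapist level, so it is not the model described. It also corresponds to a larger effect: λ = .01 × 400 × 2 / .6 = 13.3, which equals δ² / (1.2 × 4 / 400) for a difference in change of δ = .4 SD. At N = 135 it gives .56. Reading .2 as a correlation gives .98 and .64. None of these readings yields the stated result.

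Three stronger readings are tempting, and the document does not support them:

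- **That the trial cannot have 400 patients.** Planned enrolment is 423, so 400 fits, although it exceeds the 338 before the drop-out buffer. It is unattainable for NOT patients, not overall.
- **That 50 therapists are impossible.** The rule that "each therapist will treat at least eight patients and that each therapist has patients in both conditions" caps the prospective arms at 254 / 8 = 31.75, so 31 therapists. The archival IG1 patients may have had other therapists, so this cap does not bind the whole sample.
- **That .874 is wrong.** With paths of .20, the orienting calculation runs from .80 to .97 for n = 254 to 423, which brackets .874. The figure is uncheckable, not disproved.

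It is also fair that H3c and H4b do not themselves name NOT patients. H3c sits under H3, which does, and H4b uses the NOT-based awareness variable.

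**Conclusion.** The point holds in two parts. First, the stated inputs give power of .39 (between therapists), .52 to .53 (within therapist) or .59 to .61 (within therapist with a pre-score at r = .4), against .80 stated. The detectable d is .33, .27 or .25, not .2. Second, the 400 patients are about three times the 135 NOT patients expected in the analysis (400 / 135 ≈ 3.0). In that sample the detectable d is about .54 to .59 for feedback versus control, or .59 to .64 for IG2 versus CG.

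This assumes two-sided .05 throughout, equal arms for the 50 x 8 check, and a NOT share of 40%. The NOT figures treat condition as varying within therapist. If the archival IG1 patients had different therapists, therapist variance would enter the 108 vs 27 comparison, so its figures are on the favourable side. These are main-effect comparisons and do not give the power of the moderator interactions. On mediation, the finding is only that the inputs behind .874 are not given, including whether all patients or NOT patients were simulated.

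**What to change.** - Replace the d = .2 statement with the detectable effect in NOT patients, naming the comparison: IG1+IG2 versus CG, 108 vs 27 analysed (1:4, archival IG1 included), d about .54 to .59; or randomised IG2 versus CG, 54 vs 27 (1:2), d about .59 to .64. The two should not be mixed.
- If a 50 x 8 all-patient figure is kept, for instance for H3c, correct it to d about .27 (.25 with the pre-score), or .33 if condition is taken to vary between therapists.
- Remove the conclusion that the secondary analyses have sufficient power. Alternatively, state and justify the covariate R² of about .48 that the all-patient claim would need, and say that it does not carry over to NOT patients.
- State the N and path values behind .874. If all patients were simulated, re-run it on the NOT sample and report that power.
- Relabelling H3 and H4 as exploratory is optional.

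The cost is a few sentences and possibly one simulation re-run. Recruitment and the primary comparisons are unaffected, but the stated power becomes less favourable.

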## Objectives

### Primary research questions and hypotheses

The primary objective of the current project is to investigate several questions of personalized psychotherapy research with two personalized feedback intervention groups (IG1: Feedback; IG2: Feedback plus CSTs (including personalized predictions before the start of the treatment and adaptation tools during treatment) and one control group (CG) with repeated measurements. As such, this is the first study that prospectively tests the effects of personalized treatment recommendations and adaptation tools. Moreover, it adds to previous feedback research a stricter design by investigating another repeated measurement CG as well as a stricter control of treatment integrity. It also includes a structured clinical interview (SCID) and controls for comorbidity (within depression and anxiety disorders). Furthermore, a severely impaired patient sample is studied and an international outcome instrument is used. This study also investigates the above described moderators (attitudes towards, use of the feedback system, diagnoses) and mediators (therapists’ awareness of negative change and treatment length) in a comprehensive model and in one study.

Therefore, the study allows for testing the following hypotheses:Main hypotheses:H1: *NOT patients in the feedback condition (IG1) show on average better treatment outcomes than NOT patients in the CG.*
H2: *NOT patients in the IG2 (+personalized prediction and adaptation tools) show on average better treatment outcomes than NOT patients of the IG1 (no tools but psychometric feedback).*

Secondary hypotheses concerning moderators and mediators (see also Fig. 1):H3: *The positive impact of feedback for NOT patients is* moderated *through the usage of the feedback system and/or the attitudes of the therapist towards feedback.*

*H3a: The more frequently and the longer feedback is used, the more aware are therapists for negative change.*

*H3b: The more positive the therapists’ attitudes towards feedback, the more aware are therapists for negative change.*

*H3c: The effects of feedback on patient outcomes do not differ between diagnostic groups (depression and anxiety).*

H4: *The positive impact of feedback for NOT patients is* mediated *through therapists’ awareness of negative change as well as treatment length.*

*H4a: The positive impact of feedback for NOT patients is mediated by the therapists’ awareness of negative developments of their patients.*

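### The minimal detectable effect of d = .2 at 80% power for the secondary multilevel analyses does not follow from the inputs printed with it; they give about 53% power and a detectable d of about .27

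*Protocol article*

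**What the plan says.** All of this is in the protocol article, mostly in the section on sample size calculation and data analyses.

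- Optimal Design "was used to determine the minimal effect that can be detected with sufficient power, given the sample size calculation above".
- The inputs are: "Assuming a therapist effect of 5% and k = 50 therapists delivering the treatments to j = 8 patients each".
- The result is stated as: "j = 8 patients each, a small effect (d = .2) can be detected with sufficient power (1-β = .8").
- The conclusion drawn is: "Thus, given the sample size calculated for the primary hypotheses, the secondary analyses can be conducted with sufficient power using multi-level models".

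No alpha, sidedness, covariate R², allocation ratio or outcome structure is given for this calculation. The only alpha and correlation in the article belong to the G*Power calculations for H1 and H2: "an a priori significance level of .05, and a correlation between assessments of .4".

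On the level of allocation, the Randomization section says: "This means that the same therapist treats patients who are in the CG as well as patients who are in the IG2". The Discussion nevertheless calls the trial cluster randomised.

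Table 2 plans 169 + 169 patients with feedback and 85 without. The secondary hypotheses H3 and H4 open with "The positive impact of feedback for NOT patients is" moderated or mediated by other variables. H3c predicts that feedback effects are the same in depression and anxiety.

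A separate Mplus simulation reports power of .874 for the mediation models.

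**The concern.** Number of therapists, patients per therapist and therapist variance are the usual inputs to a two-level power calculation, so the result can be checked directly. Four hundred patients in two equal groups is well short of what d = .2 normally needs at 80% power, and a therapist effect of 5% removes only 5% of the variance from a within-therapist comparison.

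The figure matters because the next sentence rests on it. The Background criticises earlier moderator and mediator work for lacking specific power analyses, so this calculation supports a claimed advance. H3c raises the stakes: it predicts no difference between diagnostic groups, so a non-significant interaction could be taken as confirmation. A printed statement of adequate power would lend that reading support the design does not provide.

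**Working it through.** **Inputs.** From the article: k = 50 therapists, j = 8 patients each (N = 400), therapist share of variance ρ = .05, d = .2, target power .80. Assumed: alpha .05 two-sided, with one-sided also tried; equal groups, which is the most favourable split; total variance 1. Powers and detectable effects use the noncentral t distribution. The multiplier 1.96 + 0.84 = 2.80 reproduces the detectable effects to within about .01.

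**What the stated figure requires.** For d = .2 to have 80% power, the standard error must be about .2/2.80 = .071.

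**What the inputs give.**

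1. *Patients allocated within therapist* (the Randomization section). SE = √[4(1 − ρ)/(kj)] = √(4 × .95/400) = .0975. Power at d = .2 is .534 two-sided and .657 one-sided. Detectable d = 2.80 × .0975 ≈ .27.
2. *Adding a pre-score at r = .4.* R² = .16, so SE = .0975 × √.84 = .0893. Power is .61 and detectable d about .25. One-sided testing as well gives .72.
3. *Allocation by therapist* (the Discussion's label). SE = 2√[(ρ + (1 − ρ)/j)/k] = 2√[(.05 + .95/8)/50] = .116. Power is .39 and detectable d about .33.
4. *All 423 planned patients, equal groups, within therapist.* SE = √(4 × .95/423) = .0948. Power is .54 to .56 and detectable d about .27.

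None of these reaches .80.

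**What would reach it.**

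- Sample size: 4 × .95 × 2.80²/.2² ≈ 745, or 748 with the t distribution, against 423 planned.
- Covariates at N = 400: 1 − (.0714/.0975)² ≈ .46, or .467 with the t distribution. That corresponds to a correlation of about .68, compared with the stated .4.
- Eight patients per group per therapist (800 patients) gives .81 to .83, but 800 patients are not available.

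**Could the convention used for H1 and H2 explain it?** The pre/post interaction convention in G*Power (f = d/2, correlation .4) does reproduce the primary sizes: N = 38 gives .807 and N = 108 gives .805. For f = .1 and 400 patients it gives .95, or .88 after a design effect of 1 + 7 × .05 = 1.35. Neither is .80, and it is not the two-level calculation described.

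**Feedback versus no feedback at the planned group sizes.** Here SE = √[.95(1/n₁ + 1/n₂)]. This treats the whole contrast as within therapist, which is favourable because IG1 comes from archival data.

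| Sample | n₁ : n₂ | SE | Detectable d |
|---|---|---|---|
| Recruited, before drop-out (Table 2) | 338 : 85 | .118 | .33 |
| After drop-out (135 + 135 v 68) | 270 : 68 | .132 | .37 |
| NOT patients after drop-out, 40% NOT rate | 108 : 27 | .210 | .59 |

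The last row depends on the NOT rate. At the 49% and 56% that the article cites from earlier studies, it becomes .59 × √(.40/.49) ≈ .53 and .59 × √(.40/.56) ≈ .50.

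**Moderation by diagnosis (H3c).** As an illustration, assume two equal diagnostic groups within a balanced 400. The difference between two subgroup effects has twice the SE of the overall effect: 2 × .0975 = .195. The detectable difference is about 2.80 × .195 ≈ .55.

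**Associations (H3a, H3b).** A slope per SD of the predictor has SE √(.95/N). At N = 400 this is .049 (detectable about .14 per SD). At 108 NOT patients with feedback it is .094 (detectable about .27).

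**The case against.** The strongest defence is that the article condenses an Optimal Design run and may omit inputs. It says the analyses adjust for initial impairment, comorbidity, clinical experience and experience with the system, and the HSCL-11 is taken at every session. The correlation of .4 belongs to another calculation and describes one covariate. With an R² of .40, power at d = .2 would be 75%; with .47, it would be 80%. This stands in part. It cannot be shown that the software was misused, only that the printed result does not follow from the printed inputs. It does not rescue the sentence, which would then omit the assumption that drives its result.

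Three stronger readings are tempting, and the documents do not support them.

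- *All secondary analyses are underpowered.* H3a and H3b are worded as associations of usage or attitude with therapist awareness. Usage of the system is not a comparison with the control group at all. Their SE per SD is half that of the balanced group contrast, so the group figures do not apply.
- *A detectable effect of .59 is the general figure for the secondary analyses.* It applies only to a feedback-versus-none contrast in NOT patients, after drop-out and at a 40% NOT rate. H3c and H4b do not repeat the NOT restriction in their own wording.
- *The mediation claim falls too.* The .874 comes from a separate simulation, which this check does not test.

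It is also fair that the sample size was set by H1 and H2 and that this calculation was a check made afterwards.

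**Conclusion.** The statement is wrong as printed. On its own inputs, d = .2 has about 53% power rather than 80%, and the detectable effect is about .27. One-sided testing (66%), a pre-score at r = .4 (61%), both together (72%) and the cluster form (39%) all fall short. This rests on alpha .05 and equal groups. The planned groups are unequal, and at 338:85 before drop-out the detectable d for feedback versus none is about .33.

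The claim of sufficient power is therefore not shown for group-contrast and group-by-moderator analyses, including H3c. An undisclosed covariate R² of about .47 would reconcile the figures, but the article states none. The consequence is confined to secondary hypotheses. The primary tests and the planned sample size do not depend on it.

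**What to change.** 1. Replace d = .2 with the detectable effect that the stated inputs give: about .27, or .25 with a pre-score at r = .4. Alternatively, keep .2 and state the covariate R², alpha, sidedness, allocation and outcome structure that produced it.
2. Add the detectable effect for feedback versus none at the recruited 338:85, labelled as before drop-out (about .33). Add that it is larger if restricted to NOT patients: about .59 at 108:27, labelled as after drop-out and at the 40% NOT rate.
3. Limit the conclusion of sufficient power to analyses for which it is shown. Withdraw it for group-contrast and group-by-moderator analyses, and say for H3c that a non-significant diagnosis interaction will not be read as evidence of no difference.
4. Leave the mediation figure of .874 as it is, and do not attach the group-contrast figures to H3a or H3b.

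The cost is wording and a less favourable printed figure. No patients, tests or procedures change.
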